#### B1: the utility effect of LAAC compared with best medical care

2.4.3

The effect of the LAAC intervention will be assessed by QALYs, determined using the EQ-5D-5L questionnaire (cf. trial data collection section). EQ-5D-5L is designed as a generic instrument for use across diseases. Because it is a preference-based index instrument, a utility value can be determined immediately from survey responses (44). The EQ-5D-5L version used in the CLOSURE-AF study has five response options available for each dimension, namely mobility, personal hygiene, general activities, pain/physical complaints, and fear/depression (33), and proved sensitive in recording changes in health-related quality of life and reducing ceiling effects (34, 45).

Assuming no differences in the utilities between groups (LAAC and best medical care) at baseline, QALYs can be calculated by multiplying the mean utility values determined by the EQ-5D-5L at different points in time with the duration of the health conditions. The difference in QALYs between groups will be analyzed by a two-sided, unpaired t-test (or Welch test), providing stronger evidence of a true difference. To determine the total incremental QALYs associated with the intervention, any QALY resulting from reduced age-specific mortality rates will also be considered.

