#### EvaClosure sample size and recruitment

2.2.2

Within the health economic evaluation, the LAAC effect on health-related quality of life compared with standard therapy will be measured in terms of utilities; considering the duration of the underlying health conditions, these will be aggregated to QALYs. A two-sided, unpaired t-test (or Welch test) must be performed to ensure that differences in QALYs found between groups are not random. According to Freeman et al. (26), the utility value for the NOAC dabigatran is 0.994 and the 10% percentile is given as 0.975. Assuming a normal distribution, this results in a standard deviation of 0.015. In the same reference, the utility value for LAAC is reported as 0.998, while the 10% percentile of 0.994 results in a standard deviation of 0.003. In combination, assuming that both intervention and control groups are equally powerful, this results in an effect size of 0.37. With a targeted power of 85% and a significance level of 5%, this results in a case number of 264 patients (or 132 per group). Assuming a loss-to-follow-up-rate of 10%, the required sample size is 294 patients (147 per group). Recruitment for EvaClosure started in January 2021 and was completed in September 2023 when the target number of cases was reached. After enrollment, patients were followed up over a period of two years, with the data collection exercise completed in November 2024.

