Because of the reduced risks of stroke and bleeding and less need for lifelong medication, we can also assume that LAAC-treated patients report a less deteriorated or even better health-related quality of life in the medium and long term compared with the control group; in other words, assuming no negative effect on life expectancy, there is an expected gain in QALYs from two years after the intervention. If there is a less pronounced increase in costs, this would make LAAC a dominant stroke prevention strategy from both SHI and societal perspectives.

It is a well-known phenomenon that clinical study results may not fully reflect real-world care outside of tightly controlled conditions of clinical trials (52). Our approach of combining trial and real-world SHI data allows us to evaluate the cost-effectiveness of LAAC compared with best medical care [including (N)OAC therapy] but also in contrast to all high-risk AF patients, regardless of their individual (drug) therapy. This largely reflects the situation in the real world, where patients may not fit criteria for standard medication or may switch therapy, making the results particularly applicable to economic decisions in a real-world setting.

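### Module B1 assumes equal baseline utilities and tests QALYs without adjustment, and its mortality sentence does not say how excess deaths with LAAC would count

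*Protocol article*

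**What the plan says.** Section 2.4.3 (module B1) of the protocol article sets out three steps.

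- **Baseline:** "Assuming no differences in the utilities between groups (LAAC and best medical care) at baseline, QALYs can be calculated" by multiplying mean EQ-5D-5L utilities at the measurement times by the time spent in the health state.
- **Test:** "The difference in QALYs between groups will be analyzed by a two-sided, unpaired t-test (or Welch test". Section 2.2.2 names the same test as the basis of the sample size.
- **Mortality:** for the total incremental QALY, "any QALY resulting from reduced age-specific mortality rates will also be considered".

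The Discussion reasons in the same direction: "assuming no negative effect on life expectancy, there is an expected gain in QALYs from two years after the intervention".

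Four other places bear on the point.

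- Sections 2.2.1 and 2.2.3: EvaClosure consists of CLOSURE-AF participants who consented to the substudy. Some consented retrospectively, as late as the 24-month visit.
- Section 2.4.4: the ICER up to five years is built on the results of modules A2 and B1.
- Table 2: difference-in-differences is listed for A1, A2 and B2, but not for B1.
- Section 2.5: none of the sensitivity analyses tests the equal-baseline assumption.

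**The concern.** Baseline utility is part of each patient's area under the utility curve and also predicts the later values. A baseline gap between arms therefore carries into the QALY difference. Where a baseline measurement exists, there is no need to assume the gap away, and ignoring it wastes precision.

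In the full randomised trial only chance imbalance and precision would be at stake. Here, membership of the analysed group depends on consent given after randomisation, in some patients up to two years after it. Willingness and ability to consent can depend on health after treatment, so selection imbalance is possible as well.

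The mortality sentence is a separate weakness. It provides for fewer deaths and is silent on more deaths with LAAC. It also does not say whether the time in a health state already ends at death. If it does, adding QALYs for reduced mortality risks counting survival twice within the observed window. If it does not, excess deaths have no stated route into the B1 result. In either case the quantity tested is not the total incremental QALY, because the mortality term comes on top of it.

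**Working it through.** **1. The plan's own sample size (section 2.2.2).** Inputs: "the utility value for the NOAC dabigatran is 0.994 and the 10% percentile is given as 0.975", and "the utility value for LAAC is reported as 0.998, while the 10% percentile of 0.994 results in a standard deviation of 0.003".

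- SD = (mean − 10th percentile)/1.2816. Control: 0.019/1.2816 = 0.0148, stated as 0.015. LAAC: 0.004/1.2816 = 0.0031, stated as 0.003.
- Effect size = 0.004/√((0.015² + 0.003²)/2) = 0.004/0.0108 = 0.37. This agrees with "this results in an effect size of 0.37".
- n per arm = 2 × (1.960 + 1.036)²/0.37² = 131.2, so 132 per arm and 264 in total. With 10% loss, 264/0.9 = 293.3, so 294.

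The stated figures reproduce. The planned utility difference is 0.998 − 0.994 = 0.004. Held for two years and undiscounted, this is 0.008 QALY.

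**2. Size of a chance baseline difference.** SE = SD × √(2/132). The documents give no EQ-5D-5L SD for this population, so 0.10 to 0.25 is an assumption.

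| SD | SE of baseline difference |
|---|---|
| 0.10 (assumed) | 0.012 |
| 0.20 (assumed) | 0.025 |
| 0.25 (assumed) | 0.031 |

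With the SDs stated in section 2.2.2, the SE is √((0.015² + 0.003²)/132) = 0.0013, and 1.96 × SE = 0.0026, which is below 0.004.

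**3. How far a baseline gap carries.** With linear interpolation (section 2.5) and six-monthly measurements over two years, the weights in years are 0.25, 0.5, 0.5, 0.5 and 0.25. Baseline has weight 0.25 and the later visits together 1.75. Assume equal SDs at all visits and a correlation of 0.5 to 0.8 between baseline and each later visit. A gap of 0.01 then shifts the unadjusted difference as follows:

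- correlation 0.5: (0.25 + 1.75 × 0.5) × 0.01 = 0.011 QALY
- correlation 0.8: (0.25 + 1.75 × 0.8) × 0.01 = 0.017 QALY

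**4. Precision gained by adjustment.** The residual variance factor is 1 − r², where r is the correlation of baseline utility with the QALY itself (assumed).

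- r = 0.5: factor 0.75, a 25% reduction; 131.2 × 0.75 gives 99 per arm for the same power.
- r = 0.7: factor 0.51, a 49% residual-variance saving; 131.2 × 0.51 gives 67 per arm.

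The variance is thus cut to between 75% and 51% of its unadjusted value.

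**5. What excess deaths would cost.** Assume deaths spread evenly over two years, so one year is lost on average, and a utility of 0.6 to 0.8. One percentage point of excess deaths costs 0.01 × 1 × 0.6 = 0.006 to 0.01 × 1 × 0.8 = 0.008 QALY, against the planned 0.008. The excess itself is hypothetical; the documents give no such figure.

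**The case against.** **Randomisation and the t-test.** Allocation in CLOSURE-AF is 1:1 and randomised. Chance imbalance is already inside the standard error of an unadjusted t-test, so it is neither a bias nor an inflation of the overall type I error. This stands. For chance imbalance the loss is one of precision; only selection through consent goes further, and its size is unknown.

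**Bias towards LAAC.** A reader might infer that B1 credits averted deaths and never charges extra ones, and so favours LAAC. The text does not support that. The sentence includes reduced mortality without excluding increased mortality, and time in a health state may already end at death, which would lower QALYs in either arm. The Discussion's remark on life expectancy is conditional. What stands is that the wording is ambiguous and names one direction only.

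**The Markov model.** Section 2.4.4 estimates risks in both claims-data groups and adjusts the final model with trial results; section 2.5 adds further scenarios. The lifetime model can therefore carry deaths in either direction. The mortality point is confined to B1 and the ICERs built on it.

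**Size.** A reader might also set a chance gap at an assumed SD of 0.20 against the planned 0.004 and report a large multiple. That ratio mixes an assumed SD with an effect planned on SDs of 0.015 and 0.003. On the plan's own SDs the gap is smaller than the effect.

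**Already planned in part.** A t-test needs patient-level QALYs, section 2.5 assumes a linear curve between measurements, and the Discussion mentions multiple imputation for non-response. The area-under-the-curve step is therefore largely implied. Covariate adjustment is often left to an analysis plan, but here the article states both the equal-baseline assumption and the unadjusted test as its method.

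**Conclusion.** The point holds as a should-fix. B1 assumes equal baseline utilities and uses an unadjusted test in a subgroup formed by consent after randomisation, and nothing elsewhere in the article adjusts B1 for baseline. The cost is lost precision, with residual variance falling to 0.75 to 0.51 of its unadjusted value if adjustment were made at r = 0.5 to 0.7. Any chance or selection imbalance also stays in the incremental QALY behind the ICER up to five years.

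The mortality sentence needs rewording because it leaves excess deaths undefined and risks double counting survival. On the assumptions shown, one percentage point of excess two-year deaths is worth 0.006 to 0.008 QALY, about the planned two-year gain, so the rule is not a detail.

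A bias in favour of LAAC is possible but not shown. The illustrations rest on assumed SDs, correlations, mean utilities and timing of deaths, and ignore discounting.

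**What to change.** 1. Delete the assumption of no baseline difference in section 2.4.3.
2. State that QALYs are computed per patient as the area under the EQ-5D-5L curve, with utility 0 from the date of death in both arms.
3. Estimate the arm difference by linear regression on randomised arm and baseline EQ-5D-5L index, with robust standard errors and a confidence interval. Keep the t-test or Welch test as unadjusted support.
4. For the observed window, replace the reduced-mortality addition with wording that counts mortality differences in either direction, once.
5. Acknowledge that patients who consented late, up to 24 months after inclusion, had to be alive at consent. Neither the regression nor the utility of 0 at death recovers deaths before consent.

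The cost is a change of text and analysis code. No larger sample is needed. No new data are needed provided a baseline EQ-5D-5L is on file for each participant; the visit schedule is in a supplement that is not shown, so this should be confirmed for retrospective participants.

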#### B2: health economic evaluation of LAAC

2.4.4

In module B2, a cost–utility analysis compares LAAC with best medical care. Based on the results of modules A2 and B1, the ICER up to five years after intervention is calculated, with QALYs serving as the main effect measure. The ICER determines the costs to SHI (perspective 1) as well as society (perspective 2) for an additional QALY gained. Depending on the underlying perspective, it will be calculated from direct and indirect costs in SHI claims data, supplemented by an analysis of FIMA data from EvaClosure study patients and QALYs derived from EvaClosure study patients as described in the previous section.

A Markov model adapted from the literature (46) will be employed to capture a lifetime horizon to assess long-term effects on costs and health-related quality of life. The transitions between different health states are linked by probabilities, and the Markov property assumes that the transition probabilities result exclusively from the current state (not from history). The parameters of the initial model (46) will be fine-tuned by SHI claims data estimates to capture probabilities for patients with high-risk AF, with risk estimates evaluated among matched populations of both treatment and control claims data groups. Further relevant parameters depending on the underlying Markov state (costs, utilities) will be derived from SHI claims data analyses and the EvaClosure primary data. Parameters that cannot be sufficiently quantified by one of these data sources may be extracted from the literature or health states may be coarsened. After completion of the CLOSURE-AF trial, clinical study results and comorbidity data of EvaClosure-enrolled patients will be used to adjust the final model.

To compare costs and health effects in different years, future costs and benefits will be discounted by an annual discount rate of 3% for SHI expenditures, indirect costs, and QALYs (47). The influence on the results will be systematically addressed in sensitivity analyses as described in the next section.

Figure 1 provides an overview of the study design, the main analyses, the two corresponding data sources, and matching criteria to ensure comparability of the SHI- and trial samples.

**Figure 1 F1:**
[figure not shown]
Study populations.

### Sensitivity analyses

2.5

Probabilistic sensitivity analyses will address model parameter uncertainty; the effects of each parameter will be analyzed according to its distribution, empirically derived from location and dispersion measures (48). The influence of the discount rate will also be addressed univariately by changing it to 0% and 5% (47). The health economic analysis assumes a linear quality-of-life curve between measurement dates; as recommended by Richardson and Manca (49), we will test the extent to which this assumption influences the results.

After completing the CLOSURE-AF trial, a sensitivity analysis will address the Markov model results by an adjusted parameterization using clinical study results to uncover any influences caused by the EvaClosure sample selection. Because influences of medical–technical progress on the modeling parameters cannot be ruled out in a lifetime horizon, further sensitivity analyses with different transition probabilities will be carried out by a deterministic scenario analysis—factoring in the CLOSURE-AF investigators' clinical expertise—in order to consider these potential effects on the results.

## Discussion

3

According to available evidence, percutaneous catheter-based LAAC can be considered a potential effective alternative to medical therapies in stroke prevention for AF patients with a high risk of bleeding or contraindications to (N)OACs (50). In the United States, almost 40,000 LAAC procedures were included in the National Cardiovascular Data Registry LAA occlusion registry between 2016 and 2018, of which the majority were performed with favorable outcomes (51), and the European Society of Cardiology recommends considering the procedure for patients with contraindications to (N)OAC therapy in its current guidelines (21). However, distinct clinical superiority and economic benefits of this intervention over the best available drug therapy (standard care) still need to be confirmed, especially in patients at high risk of stroke and bleeding, as addressed by the CLOSURE-AF trial (23). As a health economic substudy, EvaClosure explores LAAC cost-effectiveness from both SHI and societal perspectives when directly compared with the standard drug therapy.

The results from clinical trials that—among other things—consider the occurrence of bleeding or stroke events as well as cardiovascular and all-cause mortality suggest that, for patients with AF, LAAC therapy is not inferior when compared with drug treatment (50). Therefore, we assume that the one-time LAAC procedure costs are compensated over time by the annual savings on drug therapy and fewer complications (e.g., reduced number and duration of inpatient stays due to stroke) (30, 50). The evidence suggests that risks of serious events are lower in LAAC-treated patients compared with the control group, thereby reducing disability and productivity loss in a medium-term time horizon of two years. In the long term (up to five years), we expect a less pronounced increase in outpatient costs, inpatient costs, and overall direct and indirect costs in LAAC–treated patients compared with the control group.

Because of the reduced risks of stroke and bleeding and less need for lifelong medication, we can also assume that LAAC-treated patients report a less deteriorated or even better health-related quality of life in the medium and long term compared with the control group; in other words, assuming no negative effect on life expectancy, there is an expected gain in QALYs from two years after the intervention. If there is a less pronounced increase in costs, this would make LAAC a dominant stroke prevention strategy from both SHI and societal perspectives.

It is a well-known phenomenon that clinical study results may not fully reflect real-world care outside of tightly controlled conditions of clinical trials (52). Our approach of combining trial and real-world SHI data allows us to evaluate the cost-effectiveness of LAAC compared with best medical care [including (N)OAC therapy] but also in contrast to all high-risk AF patients, regardless of their individual (drug) therapy. This largely reflects the situation in the real world, where patients may not fit criteria for standard medication or may switch therapy, making the results particularly applicable to economic decisions in a real-world setting.

Nevertheless, some limitations related to the study design and the data basis must be considered. On the one hand, as with any claims data studies, our data rely on correct documentation of drug therapies, diagnosis codes, and procedures. Errors may have been made in coding, although with the combination of the data used for many of the analyses (drugs, procedure, and codes to evaluate the risk scores), this would be unlikely. On the other hand, the generalizability of the results to other healthcare systems may be limited due to the use of German SHI data. In addition, when using survey or clinical trial data, data/quality issues, for example due to item non-response, may arise and need to be addressed by adequate methods such as multiple imputation. Furthermore, EvaClosure trial participants and SHI claims data population cannot be linked directly at the individual level; to determine the highest possible comparability of costs and data on health-related quality of life, applying statistically matching EvaClosure patients and their SHI claims data counterparts will be crucial to compare primary observational variables among populations, while avoiding potential bias. As multiple data sources [e.g., claims data, survey (trial) data, or literature-based data] will be used, issues such as differences in variable definitions need to be considered. In summary, by integrating clinical and real-world data with multiple health economic evaluation approaches, this study is expected to contribute to evidence-based improvements in the care of patients with AF at high risk for stroke and bleeding.
